### Data collection methods and record-keeping

Data obtained from all participants will be recorded in the case report form. Researchers who are involved in data collection will be trained to ensure standardized procedures and guidelines for data collection. All data will be stored in a locked cabinet and then coded using a unique numerical identification system. The data will be entered into an electronic database by the researchers who will receive permission to access the database for this study. Logical checks will be performed to find missing data and inconsistencies.

### Measurements of outcomes

Measures are presented in Fig. 2.

### Primary outcome

The primary outcome measure of this study is the overall intensity of CIPN symptoms in women treated with adjuvant chemotherapy for breast cancer. A NRS will be used to assess the overall intensity of CIPN symptoms. This scale is the most widely used clinical tool and its validity has been assessed in studies on patients with cancer [33, 34]. Patients will be asked to rate their symptom intensity on an 11-point scale ranging from 0 (no symptoms) to 10 (worst possible symptoms).

### Secondary outcomes

The key secondary outcome variables include physician-rated symptom severity assessed by the Total Neuropathy Score (TNS), patient-reported CIPN symptom distress level tested with a self-rated questionnaire and, and perceived HRQOL, and the instrument for pattern identification and evaluation for CIPN.

The TNS will be used to assess the presence, severity, and location of symptoms. This scale was originally developed to evaluate diabetic neuropathy and later validated in cancer patients with peripheral neuropathy [35, 36]. The TNS can provide combined information obtained from pin-prick, vibration threshold, and nerve conduction studies. The TNS (range 0 to 40) combines 10 items of symptom scores, including sensory, motor, autonomic symptoms, pin sensibility, vibration sensibility, and deep tendon reflexes [37, 38]. Each neuropathy item will be scored by a neurologist on a 0 to 4 scale. The reliability and validity of this scale were determined in various studies in patients with CIPN [36, 37, 39].

The Functional Assessment of Cancer Therapy-Breast (FACT-B) will be administered to measure the primary domains of wellbeing (i.e., physical, social/family, emotional, and functional wellbeing) and a breast cancer-specific subscale that assesses symptoms and concerns related to breast cancer [40]. The FACT-B is a 37-item measure and has demonstrated good reliability, validity, sensitivity, and suitability for use in various international studies [41–43].

The European Organization for Research and Treatment of Cancer Quality of Life (EORTC-QLQ) Chemotherapy-Induced Peripheral Neuropathy 20 (CIPN20) will be used to evaluate patients’ experience of symptoms and functional limitations related to CIPN. This instrument consists of three subscales: (1) sensory (nine items), (2) motor (eight items), and (3) autonomic (three items) symptoms and functioning. Each item is rated on a 4-point Likert scale ranging from 1 (not at all) to 4 (very much) [8]. The CIPN20 was established as a reliable and valid measurement tool for individuals with CIPN [44, 45].

The instrument of pattern identification and evaluation for CIPN will be used to diagnose and evaluate CIPN based on the perspective of traditional oriental medicine [46]. This instrument includes 30 items, which can be divided into four patterns such as wind arthralgia, cold arthralgia, dampness arthralgia, and arthralgia of the deficiency type. All items are scored by an oriental medicine physician on a 5-point Likert scale and higher scores indicate greater distress in each CIPN pattern.

### Safety and adverse events

Patients will be interviewed at each visit for assessment and asked about the occurrence of any adverse events. All adverse events related to this clinical trial will be recorded and presented in the case report form in detail. The study investigator will report serious adverse events, including death, a life-threatening event, inpatient hospitalization or prolongation of existing hospitalization, and persistent or significant disability, to the Institutional Review Board of Human Research of the Chungnam National University Hospital. In addition, a safety analysis will be performed to identify the incidence of adverse events, serious adverse events, and the number and percentage of patients reporting at least one adverse event in each group.

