**Methods:**

This study is a single-center, randomized, placebo-controlled trial with two parallel groups and a 2-week follow-up. We will enroll 80 breast cancer patients who are newly diagnosed with CIPN after chemotherapy. Duloxetine or pregabalin will be prescribed to all participants from the initial assessment. Half of the patients will be assigned into the experimental group and the other half to the control group. The CarebandR (Piomed Inc., Seoul, Korea), a wearable wristband that generates low-frequency electrostimulation, will be administered only to the experimental group. Electrostimulation will be administered on the unilateral PC6 acupoint. A numerical rating scale will be used to assess the overall intensity of CIPN symptoms. The key secondary outcome variables include patient-reported CIPN symptom distress tested by a self-rated questionnaire, physician-rated symptom severity assessed by the Total Neuropathy Score, and HRQOL.

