### Withdrawals

Participants will be free to withdraw from the study at their own request at any time without giving reasons for their decision. Withdrawals will be documented in the case report forms and an active follow-up will be conducted to monitor the occurrence of serious adverse events throughout the entire planned period of study.

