Although it is recommended to prescribe duloxetine or pregabalin for CIPN in cancer patients, this clinical guideline does not work as a definite prevention or treatment modality [9, 13, 50]. Many studies have investigated safe, complementary treatments that have positive effects on CIPN symptoms, so invasive as well as non-invasive procedures were introduced. However, mixed results were obtained due to small sample sizes, an absence of placebo-controlled study designs, and evaluations done within a limited period [53]. This study has been designed to resolve the drawbacks of the previous studies. Specifically, a placebo control group is included in this study to ensure the effectiveness of the non-pharmacological intervention that was developed [20] because CIPN can disappear naturally by discontinuing chemotherapeutic agents that cause peripheral neuropathy [50]. Currently, there are no definite criteria or tools for evaluating CIPN [10, 37, 39]. In this study, various tools, such as the TNS [37], an instrument of pattern identification and evaluation for CIPN [46, 54], a numeral rating scale, FACT-B [55], and the EORTC QLQ-CIPN 20 questionnaire (the last item of the EORTC QLQ-CIPN 20 is omitted because of inappropriateness to female patients) will be administered to evaluate the symptoms of CIPN [6]. This study can contribute to a better understanding of CIPN-associated distress and its changing pattern or cancer-specific quality of life for individuals treated with adjuvant chemotherapy for breast cancer.

The electrostimulation device used in this study is non-invasive, portable, and easy to apply. In addition, this device is not dependent on the specific place that could be procedure or the ability of the operator. It can be applied anywhere or anytime and can be effective for a long duration without serious complications when compared to electronic acupuncture that only works for a short time [54]. All participants invited in both the experimental and sham-control groups will take either duloxetine or pregabalin as prescribed for their CIPN, and the electrostimulation device will be administered only to the experimental group. It is expected that the combination of a low-frequency electrostimulation device and pharmacological intervention (duloxetine or pregabalin) will produce synergistic effects in individuals with CIPN after breast cancer chemotherapy.

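### The recording rule covers trial-related adverse events, but the planned per-group safety table is labelled as all adverse events

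*Protocol article*

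**What the plan says.** The section on safety and adverse events in the protocol article takes non-serious events through three steps.

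- **Asking.** "Patients will be interviewed at each visit for assessment and asked about the occurrence of any adverse events". There is no limit by cause.
- **Recording.** "All adverse events related to this clinical trial will be recorded and presented in the case report form in detail". Here there is a limit by relatedness.
- **Analysis.** "a safety analysis will be performed to identify the incidence of adverse events, serious adverse events", together with "the number and percentage of patients reporting at least one adverse event in each group". Again there is no limit by cause.

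Serious events have their own provisions. The same section says "The study investigator will report serious adverse events, including death, a life-threatening event", with further categories listed, and the section on withdrawals adds that "an active follow-up will be conducted to monitor the occurrence of serious adverse events throughout the entire planned period of study". Neither sentence is restricted to related events.

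Both groups also take a background drug. The abstract states "Duloxetine or pregabalin will be prescribed to all participants from the initial assessment", and the discussion says that participants in both groups "will take either duloxetine or pregabalin as prescribed for their CIPN".

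**The concern.** The analysis can use only what the case report form holds. If the form keeps only events judged related, a table headed as patients with at least one adverse event is in fact a table of patients with at least one event judged related. Those are different quantities. An all-cause comparison between randomised groups needs no one to decide what caused an event; a related-only comparison rests on that decision for every patient.

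The decision is hard in this trial. Participants have just finished chemotherapy. Table 1 requires that they take no neuropathy medication before screening, and all are then prescribed duloxetine or pregabalin and given an active or sham device. A mild event could be put down to the device, the drug, the earlier chemotherapy or an unrelated illness. The article does not say which of these count as trial-related, or who decides.

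A later analysis plan cannot repair this, because events that were never entered cannot be tabulated. The trial status section says that recruitment was already under way at submission.

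**Working it through.** The article has no figure to reproduce. It gives no adverse event rate and no proportion of events expected to be judged related. The check is therefore one of scope.

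| Step | Section | Scope stated |
|---|---|---|
| Patient interview | Safety and adverse events | Any adverse event |
| Case report form | Safety and adverse events | Trial-related adverse events |
| Incidence of adverse events | Safety and adverse events | No limit |
| Patients with at least one event, by group | Safety and adverse events | No limit |
| Serious events to the review board | Safety and adverse events | No limit |
| Serious events after withdrawal | Withdrawals | No limit |

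1. The second row is narrower than the rows before and after it. No other sentence in the article says that unrelated non-serious events are kept.

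2. The article does not define relatedness to the trial and names no assessor and no scale. Whether a given event falls inside the second row cannot be settled from the text.

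3. By suspected cause, for non-serious events:
   - Device: inside the rule.
   - Duloxetine or pregabalin: unclear. The drug is prescribed to everyone from the initial assessment, so its side effects may well count as trial-related, but the text does not say so.
   - Earlier chemotherapy or intercurrent illness: outside the rule on the plain reading.

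4. The effect on the table can be written without assuming any rate. Let p be the true proportion of patients in a group with at least one non-serious event. Let s be the share of those patients with at least one event judged related. The table then shows p × s instead of p. Since s lies between 0 and 1, the table shows something between 0 and p, and it equals p only when s = 1.

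5. Suppose p is the same in both groups. The table then shows a difference of p × (s in the device group − s in the sham group). This is zero if events are judged alike in both groups. It is not zero if they are judged differently, even though the true proportions are equal. The article gives neither p nor s, so neither the undercount nor any difference can be given a value.

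**The case against.** The strongest objection is that the text nowhere says *only*. The recording sentence does not say that other events are discarded, and the sentences around it speak of adverse events without restriction. Read with them, the phrase could loosely mean events that arise during the trial. That reading is possible, and the restrictive one is an inference from the plain wording. But nothing in the article settles it the loose way, and if that was the intent, removing the qualifier states it correctly.

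Three stronger claims are tempting, and the article does not support them.

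- *Drug side effects would go unrecorded.* The qualifier refers to the trial, not to the device, and the drug is prescribed to all participants. Such events may well be recorded. All that can be said is that their status is undefined.
- *The randomised safety comparison is lost.* Serious events are reported and followed up without a relatedness limit, so the problem is confined to non-serious events.
- *The groups would show a spurious difference of a given size.* That needs judgements that differ by group. The randomization section keeps the code link blinded from the other members of the study team, and the intervention section describes devices identical in appearance and labelling. The sham gives no stimulus, so someone might guess the allocation, but the article does not establish this. Any percentage put on it would be invented.

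It is also fair to say that a collection window, the form's layout and the ranking of safety tables belong to fuller documents and are no fault of an article. The point here concerns a rule that the article does state, and that does not match the analysis it states in the same section.

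**Conclusion.** The point holds in limited form. For non-serious events, the recording rule as written is narrower than both the question put to patients and the planned per-group analysis. If it is followed literally, the table labelled as patients with at least one adverse event would omit events judged unrelated and would depend on an undefined causality judgement.

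This conclusion assumes that the recording sentence is applied as worded and that no instruction elsewhere widens it; the article contains none. The size is unknown and could be small if nearly every event is regarded as trial-related. Sample size and efficacy results do not depend on it. What depends on it is whether the non-serious part of the safety table measures what its label says.

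**What to change.** Delete the qualifier from the recording sentence, so that all adverse events during the trial are recorded regardless of suspected cause. Record relatedness as a separate item on the form. Report all-cause events by group as the table already planned, with the related subset alongside.

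The cost is slightly more event recording and one additional item on the form. Patients are already asked about any adverse event at each visit, so no new assessment is needed. If the phrase was meant to cover everything arising during the trial, the change alters nothing in practice and removes the doubt. It concerns data capture and reporting only, and changes nothing in how participants are treated.

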### Withdrawals

Participants will be free to withdraw from the study at their own request at any time without giving reasons for their decision. Withdrawals will be documented in the case report forms and an active follow-up will be conducted to monitor the occurrence of serious adverse events throughout the entire planned period of study.

### Data analysis

Statistical analysis will be performed using SPSS version 22 (IBM SPSS Inc., Chicago, IL, USA) software by a statistician blinded to patient allocation. The efficacy of the intervention will be analyzed using a full analysis set approach with the last-observation-carried-forward method for primary outcome. Demographic and clinical characteristics will be described as frequency and composition ratio. Categorical data will be described as frequency and percentage. Continuous data will be presented by mean and standard deviation or median and interquartile range according to whether the data are normally distributed. For comparison with the baseline outcomes between groups, continuous data will be analyzed by using independent *t* tests or Wilcoxon rank sum tests and categorical data will be analyzed by the chi-squared or Fisher’s exact test. Mean differences from baseline to post treatment in each group will be calculated to evaluate the efficacy of treatment. Analysis of covariance will be used to analyze a difference in primary and secondary outcomes between groups if the residuals are normally distributed, otherwise the Wilcoxon rank sum test will be conducted. Clinically relevant covariates will be included in these analyses. A comparison between responders and non-responders will be conducted to explore heterogeneity of any key variables. A *p* level of 0.05 (two-tailed test) will be considered to indicate statistical significance for all analyses.

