### Sample size

Sample size will be decided by the primary outcome. According to the published study on low-frequency electroacupuncture treatment for CIPN, the overall change in mean scores between baseline and 2-week follow-up was − 4.0 with a significant decrease in pain over time [27, 29]. However, there was no previous study that could provide data to compute standardized differences between two means of two groups in calculating the sample size for this trial. Accordingly, this study will evaluate the efficacy and feasibility of the low-frequency wristband intervention for patients with CIPN [30]. With consideration for the maximum number of subjects needed in pilot studies and the central limit theorem, a total sample size of 40 per group was calculated [31]. The sample size was calculated based on the changes in the NRS between baseline (visit 2) and the end of the study (visit 3). Based on two previous studies [26, 29], the mean and standard deviation are conservatively assumed. We calculated that 32 patients per group would be required to achieve a power of 95% with a two-sided significance level of *p < 0.05* for detecting the superiority of treatment with Careband R by a *t* test. Here, the assumed effect size (*d*) was 2.33. To account for possible dropouts (10%), the target number of patients was, therefore, set at 40 per group (80 in total) (see below):$$ {\displaystyle \begin{array}{l}\mathrm{n}=2\kern1em {\left\{\frac{\left({\mathrm{Z}}_{1-\upalpha /2}+{\mathrm{Z}}_{1-\upbeta}\right)\kern0.5em \ast \kern0.5em \upsigma}{\varDelta}\right\}}^2\\ {}\mathrm{n}=2\kern1em {\left\{\frac{\left(1.96+1.64\right)\kern0.5em \ast \kern0.5em 2.57}{2.33}\right\}}^2\\ {}\mathrm{n}=31.63\end{array}} $$

*H*_*0*_: *d*_*t*_ *= d*_*c;*_
*H*_*1*_: *d*_*t*_ *≠ d*_*c*_*;* d_*t*_: the changes in the NRS between baseline (visit 2) and the end of the study (visit 3) of the intervention group; *d*_*c*_: the changes in the NRS between baseline (visit 2) and the end of the study (visit 3) of the control group; *Δ*; *d*_*t*_ − *d*_*c*_.

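### Comparing responders with non-responders cannot show whether the device effect differs between patients; exploratory treatment-by-baseline interactions in the planned ANCOVA can address it

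*Protocol article*

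**What the plan says.** Three sentences in the Data analysis section of the protocol article matter here.

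- On change within arms: "Mean differences from baseline to post treatment in each group will be calculated to evaluate the efficacy of treatment".
- On the randomised comparison, directly afterwards: "Analysis of covariance will be used to analyze a difference in primary and secondary outcomes between groups if the residuals are normally distributed". A Wilcoxon rank sum test is the fallback, and "Clinically relevant covariates will be included in these analyses".
- On heterogeneity: "A comparison between responders and non-responders will be conducted to explore heterogeneity of any key variables".

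The section closes with a general rule that a "level of 0.05 (two-tailed test) will be considered to indicate statistical significance for all analyses".

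The Sample size section sets the hypotheses on the difference between arms in NRS change, Δ = d_t − d_c. Other sections describe what happens to patients in both arms. Everyone is prescribed duloxetine or pregabalin from the initial assessment (Abstract, Methods), and nobody may have taken neuropathy medication before screening (Table 1). Entry needs a score of at least 5 (Participants). The Discussion justifies the placebo arm on the ground that "CIPN can disappear naturally by discontinuing chemotherapeutic agents that cause peripheral neuropathy".

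**The concern.** Whether a patient is a responder is known only after treatment, and it depends on everything that moves the NRS score, not on the device alone. In this trial at least four things besides the device can lower the score over two weeks: a newly started drug, recovery after chemotherapy ends, placebo response, and regression to the mean after selection on a high score. A baseline variable linked to any of these will differ between responders and non-responders even if the device does nothing.

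The comparison fails for this purpose however it is carried out. If both arms are pooled, it describes who improves under either wristband. If it is confined to the device arm, it has no control and still describes who improves. In neither case does it estimate how the difference between device and sham varies with a patient characteristic, which is what heterogeneity of the device effect means.

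The risk is that a prognostic factor is reported as marking the patients who benefit from the device and is then used to select patients for a later trial or for practice.

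A smaller concern is that attaching the word efficacy to the change in each arm blurs which result decides the efficacy question.

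**Working it through.** **1. The plan's own figure.** Inputs from the Sample size section: difference 2.33, SD 2.57, two-sided 5% level, 95% power.

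n = 2 × {(1.96 + 1.64) × 2.57 / 2.33}² = 31.53; with 1.645 in place of 1.64 it is 31.62. The article prints 31.63. All round up to 32 per group, so the stated number reproduces. It rests on a between-arm difference.

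**2. What the responder comparison shows when the device does nothing.** The article gives no response cut-off and no recovery rates, so the following are assumptions: response is a fall of at least 2 NRS points; half the patients carry a baseline variable X; carriers improve by 2.0 points on average in both arms; non-carriers improve by less; changes are normal with SD 2.57. The device effect is zero, so X is purely prognostic.

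P(response | X) = Φ((2.0 − 2)/2.57) = 0.500.
P(response | no X) = Φ((m − 2)/2.57), where m is the non-carriers' mean improvement.
Share of responders with X = 0.500 / (0.500 + P(response | no X)).
Share of non-responders with X = 0.500 / (0.500 + 1 − P(response | no X)).

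| m (assumed) | P(response, no X) | X among responders | X among non-responders | Gap (percentage points) |
|---|---|---|---|---|
| 1.5 | 0.423 | 54.2% | 46.4% | about 8 |
| 1.0 | 0.349 | 58.9% | 43.4% | about 15 |
| 0.5 | 0.280 | 64.1% | 41.0% | about 23 |

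Raising the assumed cut-off to 3 points gives gaps of about 8, 16 and 24. The treatment-by-X interaction is zero throughout, because X shifts both arms equally. The gap therefore says nothing about the device.

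**3. Precision of the better method.** Take 40 per arm, SD 2.57 and a baseline variable split evenly, giving 20 patients per cell.

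- SE of the main effect = 2.57 × √(2/40) = 0.57; 95% half-width 1.96 × 0.575 = 1.13.
- SE of the interaction = 2.57 × √(4/20) = 1.15; 95% half-width 1.96 × 1.149 = 2.25.

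The interaction half-width is twice that of the main effect and about the size of the whole planned difference of 2.33. At the protocol's own level and power, the interaction would have to be (1.96 + 1.64) × 1.149 = 4.14 points. These figures ignore dropout, which widens them, and any gain from covariate adjustment, which narrows them.

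**4. Why the word efficacy should not attach to change within an arm.** Assume no device effect, 40 per arm, SD of change 2.57, and a common improvement in both arms of 0.5, 1.0, 1.5 or 2.0 points. A one-arm test of change would be significant with probability 0.22, 0.67, 0.95 or 1.00, while the between-arm test stays at 0.05. No one-arm test is named in the article; this only illustrates why the change within an arm should be labelled descriptive.

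**The case against.** The best defence of the responder sentence is that it only sets out to explore. It does not claim to identify effect modifiers, a description of how responders differ is common, and the responder definition may stand in a fuller document that is not shown. Part of this stands: the missing definition is not a finding, and the analysis carries no confirmatory weight. But calling the analysis exploratory does not make it able to address heterogeneity of the device effect. The 5% rule for all analyses also makes no exception for it.

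A second objection is that interactions in 80 patients will be imprecise. That is correct, as step 3 of the working shows. It is a reason to keep the list short and report intervals. It does not favour a comparison that estimates something else.

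A reader might also infer a stronger point from the sentence on mean changes: that efficacy is to be judged within arms and that the plan lacks a valid test of the device. The document does not support this. The next sentence plans a between-group ANCOVA, the hypotheses and sample size concern Δ = d_t − d_c, and no paired or one-arm test is named. The per-arm changes can be read as the two quantities that the ANCOVA then compares. The Discussion shows that the authors included the placebo arm because of natural recovery. Nor can the published change of 4.0 points be set against the planned 2.33 to say how much of a within-arm fall is not due to the device, because the article does not link the two figures in that way.

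**Conclusion.** The point holds for heterogeneity. The planned comparison groups patients by post-randomisation outcome and cannot separate prognosis from device effect. This follows from the design and needs no numerical assumption. The gaps of about 8 to 23 percentage points with zero device effect show the possible size and depend on the assumed cut-off, recovery rates and share of carriers.

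For efficacy, only a wording point remains. The protocol contains a valid randomised comparison and is sized on it; 32 per group reproduces. No planned figure or primary analysis changes. The correction is worth making because the present method could yield a misleading account of who benefits. It does not threaten the main result.

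**What to change.** Replace the responder sentence with two exploratory analyses:

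- the proportion of responders compared between the randomised arms, using one cut-off fixed before unblinding;
- treatment-by-baseline-variable interactions in the ANCOVA already planned, for a short list named in advance (for example drug stratum, baseline NRS and age), reported as estimates with 95% confidence intervals.

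As a minor edit, say that mean changes in each arm are descriptive and carry no p values, and that the efficacy conclusion rests on the between-group ANCOVA estimate with its 95% confidence interval.

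The cost is a few sentences and little extra analysis. The trial needs no new data and no more patients. Recruitment was ongoing when the article was submitted; the change should be made before the data are unblinded. The drawback is imprecise interaction estimates with 80 patients, which the plan should state so that a wide interval is not read as evidence that the effect is uniform.
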